#### Pretesting and Pilot Testing

Prior to fielding, the DCE surveys will be pretested and iteratively revised using cognitive interviews. Participants will be asked to “think aloud” while completing the DCE survey; interviewers will evaluate understanding and probe why selected answers were chosen. We will pay particular attention to the framing and cultural responsiveness of the selected attributes and levels during the cognitive interviews. Our research team has substantial experience with the development, deployment, and analysis of DCEs, and the development of this particular DCE survey will benefit from lessons learned in our prior DCEs [35-38]. Two members of the research team (RB, TL) are members of the Lumbee Tribe and conduct cancer prevention research with Lumbee Tribal members.

#### Supplemental Survey

Participants will also complete a survey that assesses potential correlates of preferences. The survey will elicit sociodemographic characteristics (eg, age), health-related quality of life, trust in providers, decisional control preferences, and fatalism (see phase 2).

#### Sample Size and Statistical Power

Based on our past experience and DCE sample size recommendations, which combine the number of respondents (n), choice tasks (t=10), alternatives per task (a=2), and the maximum number of feature levels (c=4), and established a cutoff (nta/c≥500), we calculated that a sample size of 100 participants will provide sufficient power to characterize mean preferences for PC screening [39].

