#### Experimental Design and Choice Set Construction

Each respondent will be asked to complete 10 choice tasks. The attributes that will be tested include: (1) chance of dying from PC, (2) screening interval, (3) side effects of PC treatment, (4) risk of false positives, and (5) chance of finding harmful cancer. We will use 2 choice tasks designed to monitor attention and ensure participants understand the choice tasks; the first choice task will include a dominant choice and will be repeated halfway through the set of choice tasks. Robust statistical results can be obtained from a fractional factorial design of several dozen questions. Formally, we will use Ngene software (Sydney, Australia) to identify a *d*-efficient, partial factorial design that has good attribute-level balance to ensure that each respondent will see most or all attribute levels. To incorporate preference heterogeneity into the statistical design, the design will be optimized for mixed multinomial logit analysis, with simulations drawing priors from the estimated parameter distributions, which will be initially based on directional hypotheses and updated using relevant information from the phase 2 data. We will use a panel random parameter logit model to account for the inherent panel nature, with 500 Halton draws and normally distributed random parameters. Due to the anticipated small sample size, we will not implement blocking. We will use SurveyEngine survey software to design and host the final DCE. We will only include participants in the analyses if they answered all of the choice tasks.

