#### DCE Questionnaire Fielding

We will work with the Lumbee Tribe to distribute the online survey and advertise it to Lumbee men. Specifically, we will use a combination of social media, direct emails, flyers, and advertisements at provider offices, and participation in cultural events. Assuming a 25% response rate to the online survey [40], we will distribute the online DCE survey to 400 American Indian men in the Lumbee Tribe in order to reach 100 completed surveys.

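### The sample-size index counts all 10 choice tasks, but on the plain reading two are a dominant-choice check and its repeat; with 8 informative tasks it is 400, not 500

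*Protocol article*

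**What the plan says.** Under Sample Size and Statistical Power, the protocol article takes "choice tasks (t=10), alternatives per task (a=2), and the maximum number of feature levels (c=4", says that it "established a cutoff (nta/c≥500", and concludes that "a sample size of 100 participants will provide sufficient power to characterize mean preferences for PC screening". It cites past experience alongside the rule, but the rule supplies the only figures.

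The task count is set under Experimental Design and Choice Set Construction: "Each respondent will be asked to complete 10 choice tasks". The same paragraph then says "We will use 2 choice tasks designed to monitor attention and ensure participants understand the choice tasks", and describes them: "the first choice task will include a dominant choice and will be repeated halfway through the set of choice tasks". It adds: "Due to the anticipated small sample size, we will not implement blocking". Every man therefore sees the same set of tasks.

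Under DCE Questionnaire Fielding, the recruitment target follows from the 100: "we will distribute the online DCE survey to 400 American Indian men in the Lumbee Tribe in order to reach 100 completed surveys".

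**The concern.** In this rule, t stands for the choice tasks from which preference weights are learned. A task with a dominant option asks for no compromise between attributes, so an attentive man's answer says almost nothing about their relative weights. Repeating the same task tests consistency and adds no new comparison. The article itself explains, at the start of Phase 3, that the method works by making respondents trade preferred features against less preferred ones.

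If the check and its repeat are two of the 10 tasks, entering t = 10 counts them at full weight. Because the index lands exactly on the cutoff, nothing can absorb the difference. What is at stake is the stated property of the design: that 100 men satisfy the chosen rule and that this shows sufficient power for mean preferences.

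**Working it through.** **Inputs, all from the protocol article**

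| Quantity | Value | Section |
|---|---|---|
| Respondents, n | 100 | Sample Size and Statistical Power |
| Tasks entered in the rule, t | 10 | Sample Size and Statistical Power |
| Alternatives per task, a | 2 | Sample Size and Statistical Power |
| Maximum levels, c | 4 | Sample Size and Statistical Power |
| Cutoff for nta/c | 500 | Sample Size and Statistical Power |
| Tasks each man completes | 10 | Experimental Design and Choice Set Construction |
| Check tasks | 2 (first task and its repeat) | Experimental Design and Choice Set Construction |
| Response rate | 25% of 400 invited | DCE Questionnaire Fielding |

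**Step 1. Reproduce the stated figure.** Index = n × t × a / c = 100 × 10 × 2 / 4 = 500. Required n = 500 × c / (t × a) = 500 × 4 / (10 × 2) = 100. The plan's arithmetic is correct for the inputs it uses, and the margin is zero.

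**Step 2. Count the tasks.** The figure of 10 is given as what each respondent completes. The check is described as the first choice task and its repeat as falling halfway through the set, so both sit among the tasks and not before them. A separate training and comprehension task, completed before the choice tasks, is described under Choice Context and Hypothesis, so the check is not that warm-up. No section gives a total of 12. On this reading, 10 − 2 = 8 tasks involve a trade-off.

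**Step 3. Recompute with t = 8.** Index = 100 × 8 × 2 / 4 = 400. The shortfall is (500 − 400) / 500 = 20%. Meeting the rule by numbers alone would take 500 × 4 / (8 × 2) = 125 men, or 125 / 0.25 = 500 invitations instead of 400.

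**Step 4. Vary the assumptions, with n = 100.**

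| Reading | t | a | c | Index | n needed for 500 |
|---|---|---|---|---|---|
| As stated, or checks additional to the 10 | 10 | 2 | 4 | 500 | 100 |
| Only the repeat discounted | 9 | 2 | 4 | 450 | 112 |
| Check and repeat both discounted | 8 | 2 | 4 | 400 | 125 |
| Both discounted, at most 3 levels | 8 | 2 | 3 | 533 | 94 |
| Both discounted, opt-out counted as an alternative | 8 | 3 | 4 | 600 | 84 |

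With the plan's own a = 2 and c = 4, losing even one task takes the index below the cutoff. The last two rows change inputs that the plan has stated.

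**The case against.** The strongest reply is that the article never says outright that the two checks are among the 10. Their described positions, first and halfway, would fit a survey of 12 tasks as well as one of 10. If 12 was intended, t = 10 and the index of 500 are both right. This stands as a possibility, and it is why the conclusion is conditional. The task total in the design section would then be understated and would still need correcting.

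Second, nothing says that the checks are dropped from the model, and the rule as printed counts choice tasks without excluding any. That is true. But keeping the checks in the model does not give them trade-off content, so counting them in full still overstates the index.

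Third, c = 4 is provisional. The attributes and levels will be guided by Phase 2, which is still under way, and with at most 3 levels the index passes at t = 8. This stands, and the fix allows for it.

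Fourth, the example task in Table 2 shows three options, and a = 3 would give 600. The sample-size section fixes a = 2, however, and DCE Data Analysis codes one alternative against the other. The check here applies the rule as the plan states it.

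A reader might infer more: that the plan definitely fails its own criterion, that the index is the sole justification for 100 men, or that 125 men must be recruited. The documents support none of these. Whether the checks fall inside the 10 is inferred from the wording, past experience is cited as well, and the gap can be closed without recruiting anyone.

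**Conclusion.** The concern holds in conditional form. On the most natural reading, the design gives 8 informative tasks per man and an index of 400 against a cutoff of 500, so the only quantified support for sufficient power is not met.

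This rests on three assumptions: the two checks are within the 10, a dominant task and its repeat should not count towards t, and the plan's a = 2 and c = 4 stay as stated. If the checks are additional to the 10, the index of 500 stands and only the description of the survey needs correcting.

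The multiplication itself is not wrong; the question is which t belongs in it. Nor does an index of 400 measure a loss of precision or power. The rule is a rule of thumb with no effect size or variance behind it, so the shortfall shows only that the stated criterion is not reached. The two sections need reconciling on either reading.

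**What to change.** Keep n = 100. Field 10 designed tasks plus 2 check tasks, state the total of 12 under Experimental Design and Choice Set Construction, and say that the checks are not counted in t. The sample-size section is then true as written. The cost is two extra screens per man, or one clarifying sentence if 12 tasks were already intended. The Results section reports that no one has yet been recruited into the choice experiment, so the change can still be made.

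If the survey is to stay at 10 tasks including the checks, restate the sample-size section as t = 8, index 400, below the cutoff of 500, and withdraw the statement that the cutoff shows sufficient power. This costs only a less favourable figure.

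If Phase 2 leads to a final design with at most 3 levels per attribute, restate the index as 100 × 8 × 2 / 3 = 533. Levels need not be capped merely to satisfy the rule. The index also does not show that 8 unblocked tasks can support all the level effects, so that should be confirmed when the design is generated.

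### The 100-man sample meets the plan's cutoff only if all 10 choice tasks are informative; on the natural reading two are attention checks, which gives 400 against 500

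*Protocol article*

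**What the plan says.** Two sections of the protocol article bear on this.

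*Sample Size and Statistical Power* combines the number of respondents with "choice tasks (t=10), alternatives per task (a=2), and the maximum number of feature levels (c=4" and says that the authors "established a cutoff (nta/c≥500". From this it concludes that "we calculated that a sample size of 100 participants will provide sufficient power to characterize mean preferences for PC screening".

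*Experimental Design and Choice Set Construction* says "Each respondent will be asked to complete 10 choice tasks". It then describes two tasks that monitor attention and understanding: "the first choice task will include a dominant choice and will be repeated halfway through the set of choice tasks". It does not say outright whether these two belong to the 10 or come on top of them. It also says that the design will not be blocked, so all men see the same tasks.

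**The concern.** A rule that counts tasks treats each one as an equal contribution to the preference estimates. A task with a dominant option does not contribute in that way. An attentive respondent picks the better option whatever weight he gives to each attribute, so his answer shows that he understood the task but not what he would give up for what. Repeating the task tests consistency and adds no new trade-off.

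If both checks sit inside the 10, then 2 of every man's 10 answers, or 200 of the 1,000 task responses from 100 men, serve quality control rather than estimation. The sample size section counts all 1,000. Because the stated calculation lands exactly on its cutoff, any such loss takes it below.

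This rule is the only justification given for n = 100, and the article presents its result as a statement about power. A later report could then claim a power that was never worked out, resting on a criterion that the fielded survey may not meet.

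**Working it through.** **Inputs** (all from *Sample Size and Statistical Power* unless noted)

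- n = 100 respondents
- t = 10 tasks; *Experimental Design* also gives 10 tasks per respondent
- a = 2: "alternatives per task (a=2"
- c = 4: "the maximum number of feature levels (c=4"
- cutoff: nta/c ≥ 500
- check tasks: 2 (*Experimental Design*)
- response rate: 25% (*DCE Questionnaire Fielding*)

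**Step 1. Reproduce the plan's figure.** The index is n × t × a / c = 100 × 10 × 2 / 4 = 500. Solved for n, 500 × 4 / (10 × 2) = 100. The stated sample size is reproduced exactly, with no slack.

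**Step 2. Decide what t should be.** *Experimental Design* gives the total of 10 and then places one check as the opening task and the other midway through the set. The only set described is the set of 10, so the natural reading puts both checks inside it. That leaves 10 − 2 = 8 trade-off tasks. The text does not exclude the other reading, so all cases are shown.

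| Reading | t | Index at n = 100 | n needed, 500 × 4 / (t × 2) | Invitations at 25% |
|---|---|---|---|---|
| Both checks inside the 10, neither counted | 8 | 100 × 8 × 2 / 4 = 400 | 125 | 500 |
| Only the repeat discounted | 9 | 100 × 9 × 2 / 4 = 450 | 111.1, so 112 | 448 |
| Checks additional to the 10 | 10 | 500 | 100 | 400 |

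On the first reading the shortfall is (500 − 400) / 500 = 20%. On the second it is 10%. On the third there is none, and no margin either.

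**Step 3. Effect on precision.** If standard errors fell with the square root of the number of informative tasks, going from 10 to 8 would raise them by a factor of √(10/8) = 1.118, or about 12%. This is an upper bound. In the planned panel mixed logit, the variance of a mean preference has roughly the form (B + W/t)/n, where B is variation between men and W is choice noise within a man. B does not shrink as t grows, so whenever B > 0 the ratio is below √(10/8). The documents give neither B nor W, so no closer figure can be stated.

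**Step 4. Can the rule yield power?** Its inputs are n, t, a and c. Power for a preference weight also needs the size of the weight, its variance under the model and a significance level. None of these enters the rule, so meeting the cutoff does not imply any particular power. This step does not depend on how Step 2 is resolved.

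**The case against.** **The checks may be extra.** The article never says that the two checks are among the 10. If they are additional, t = 10 is correct and the cutoff is met. This stands, and it makes the shortfall conditional. It does not remove the problem: t is the input that decides whether the criterion is met, and the article leaves it open between a reading that fails and one that passes with nothing to spare.

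**The other inputs could rescue the figure.** The final attributes and levels await Phase 2. With at most 3 levels, 8 tasks give 100 × 8 × 2 / 3 = 533. The example task in Table 2 has three columns, and counting the opt-out as a third alternative gives 100 × 8 × 3 / 4 = 600. Both figures pass. However, the sample size section fixes 2 alternatives and 4 levels, and *DCE Data Analysis* codes the preferred option against a single other one. Neither rescue is available without changing the stated inputs. What stands is that the index should be recalculated if Phase 2 changes the levels.

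**The power wording is editorial.** The rule and its inputs are shown openly, the claim is limited to mean preferences, and the Discussion lists the small sample as a limitation. All true. The sentence still makes a positive claim that its inputs cannot carry.

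**Handling of the checks in the model may be set out elsewhere.** A full protocol or analysis plan may say that they are left out of estimation. The article's silence on this is therefore not a fault in itself. The count of tasks in the sample size formula is stated in the article and can be judged there.

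**Conclusion.** The point holds in a conditional form. With the plan's own 2 alternatives and 4 levels, and the two checks inside the 10 tasks as the text most naturally reads, 100 men give an index of 400 against a cutoff of 500. The result assumes that a dominant task and its repeat carry little or no trade-off information. Discounting only the repeat gives 450, which still fails. If the checks are additional, the index is exactly 500. The power claim is unsupported in every case.

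Some stronger readings are tempting but go beyond the documents:

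- A reader might infer an arithmetic mistake, or a definite failure of the criterion. The calculation as printed is correct, and the failure depends on a reading that the text favours but does not fix.
- A reader might take 12% as the loss of precision. It is only a ceiling.
- A reader might infer that recruitment is set too low, because the team says "we will distribute the online DCE survey to 400 American Indian men in the Lumbee Tribe in order to reach 100 completed surveys" and 400 × 25% is exactly 100. An expected yield equal to the target is not an error, the 400 is not stated as a cap, and the analysis section allows for more than 100 responses.
- A reader might infer further losses from men who fail the checks, or a weakness in the checks from where the options are placed. The article states no exclusion for failed checks and gives no option positions, so neither can be argued from it.

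**What to change.** State whether the two checks are within or beyond the 10 tasks, and then take one of two routes.

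1. **Field 12 tasks:** 10 from the experimental design plus the 2 checks, with the checks left out of the mixed logit. Then t = 10 is right and n = 100 gives 500, still exactly on the cutoff.
2. **Keep 10 tasks in total:** use t = 8 in the formula and restate the index as 400, below the cutoff. Meeting the cutoff with 8 tasks would instead take 125 men, or 500 invitations at the assumed 25% response.

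Under either route, replace the statement about power with one saying that the rule of thumb for main effects is, or is not, met.

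The first route costs two more short tasks per respondent. Only men who answer every task are analysed, so a longer survey could lose a few more; the documents give no figure for this. The second route costs a less favourable stated figure. The article reports that nobody has yet been recruited into the DCE, so either change can be made before fielding.

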#### DCE Questionnaire Fielding

We will work with the Lumbee Tribe to distribute the online survey and advertise it to Lumbee men. Specifically, we will use a combination of social media, direct emails, flyers, and advertisements at provider offices, and participation in cultural events. Assuming a 25% response rate to the online survey [40], we will distribute the online DCE survey to 400 American Indian men in the Lumbee Tribe in order to reach 100 completed surveys.

#### DCE Data Analysis

We will analyze the choice data using mixed (random parameter) logit models [20]. The binary dependent variable will be 1 for the more preferred alternative and 0 for the other alternative in each choice task. The independent variables will be the effects-coded levels of each attribute. The mixed logit specification, estimated in STATA (StataCorp) version 16 or higher, allows for variation in preferences across respondents as well as error correlation across choice tasks within respondents. If we obtain more than 100 responses, we will also test latent class models to analyze the data, which may provide a better model fit. Latent class models will be estimated using Latent Gold Choice 5.0 software (Statistical Innovations).

The preference weights estimated using mixed logit models are the primary outcome of phase 3. Positive parameter estimates for effects-coded attribute levels indicate that an attribute level is more preferred compared to the mean, while negative parameter estimates indicate aversion. Tradeoffs will be described in the form of mRS.

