### Choice Context and Hypothesis

The study aims to identify the key considerations that American Indian men make when deciding about whether to get screened for PC. The choice context presented to the participants in the DCE will be framed as follows:

*Your doctor informs you that there is a blood-based test for PC, and that you are eligible for this test due to your age. Please consider the following scenarios. In which of these scenarios would you be more likely to test for PC?*

We hypothesize that American Indian men evaluate several screening attributes, such as mortality benefit, unnecessary biopsies, and treatment, as well as contextual factors, such as experiences with PC and the manner in which information is presented, when considering PC screening [25].

DCE choice tasks will resemble the task shown in Table 2. The sample task includes attribute levels identified in the literature review and several attribute levels hypothesized a priori to influence the choices of American Indian men; the selection of attributes and attribute levels in the actual DCE will be guided by the findings from phase 2. Columns represent screening options. Rows describe the attributes identified in phase 2. Cells represent feasible levels for each attribute. Each choice task involves the comparison of 2 hypothetical PC screening tests, followed by an “opt-out” question, that is, whether the participant would get tested in the preferred scenario, which reflects a realistic choice based on current USPSTF PC screening recommendations [10]. This opt-out option provides a reference point that allows for estimates of the potential uptake of PC screening. Prior to the choice tasks, participants will be introduced to each attribute, presented with *ceteris paribus* conditions (eg, the participant has insurance that covers the test), and will complete a training and comprehension task.

**Table 2. T2:** Example of discrete choice experiment choice task.

Attribute	Option A	Option B	Option C
Chance of identifying PC^a^ after it has spread	100 out of 1000 men like you would have PC diagnosed after it has spread	200 out of 1000 men like you would have PC diagnosed after it has spread	N/A^b^

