Relative risk reduction of PC death from getting screened	Getting screened for PC would reduce the chance that you die because of PC by 25%	Getting screened for PC would reduce the chance that you die because of PC by 10%	Your chance of dying because of PC as a result of not getting screened is about 4%
Risk of false positive	4.6 men like you who get the test would have a biopsy from a false positive test result	2.3 men like you who get the test would have a biopsy from a false positive test result	N/A
Health care provider suggestion	Your doctor asks you whether you want to get screened	Your doctor suggests you get screened	Your doctor asks you whether you want to get screened
Which option do you prefer?	Option A	Option B	Option C

a PC: prostate cancer.

b Not applicable.

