### Outcome Measure

#### Primary and Secondary Outcomes

The main survey outcome of interest is the PC screening uptake, and the main analytic outcome is the association between each attribute level and the probability of PC screening uptake. The secondary outcome, which is the tradeoffs that American Indian men are willing to make when deciding about PC screening, will be described in the form of mRS. Results will be used to estimate participants’ relative preferences for all potential combinations of attribute levels, that is, PC screening. Feasible strategies can be ranked in terms of expected PC screening uptake, providing concrete guidance on the acceptability of alternative scenarios, and prioritizing specific strategies to increase PC screening uptake in Lumbee men.

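### The choice model as written has no no-test alternative, so it yields preference weights but not the uptake probabilities that are the main analytic outcome; the response format and the primary outcome are also stated inconsistently

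*Protocol article*

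**What the plan says.** All references are to the Protocol article.

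- **Primary and Secondary Outcomes.** Two main outcomes are set. On the survey side: "The main survey outcome of interest is the PC screening uptake". On the modelling side, the section states that "the main analytic outcome is the association between each attribute level and the probability of PC screening uptake". It adds that "Feasible strategies can be ranked in terms of expected PC screening uptake".
- **Choice Context and Hypothesis, text.** Each task compares two hypothetical tests. A second question then asks "whether the participant would get tested in the preferred scenario". The stated purpose is explicit: "This opt-out option provides a reference point that allows for estimates of the potential uptake of PC screening".
- **Table 2.** Option C is a third column with entries of its own, two of them marked not applicable. One question, "Which option do you prefer", takes A, B or C as the answer.
- **DCE Data Analysis.** The response is coded as follows: "The binary dependent variable will be 1 for the more preferred alternative and 0 for the other alternative in each choice task". Attribute levels, effects-coded, are the only predictors named. The section then gives the mixed-logit preference weights as the primary outcome of phase 3.
- **Sample Size and Statistical Power.** The rule of thumb is applied with two alternatives per task, so the opt-out is not counted.

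**The concern.** Uptake is a comparison between being tested and not being tested. The outcome section needs that comparison and the choice-task section collects it, but the analysis section specifies a model of one test against the other. Followed literally, the model shows which of two screening scenarios a man prefers, including a man who would accept neither. It does not show how likely he is to be tested, or how far an attribute level moves that likelihood.

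Two inconsistencies add to this. The two response formats produce different data and need different likelihoods. Under the single A/B/C question, a man who picks C states no preference between A and B, so the 1/0 coding has no place for him. Also, uptake is the main outcome in one section and preference weights are primary in another, so it is unclear which result the study will be judged on.

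The opt-out is unlikely to be marginal. The protocol's own review (Table 1) reports it for 4.6% of men in one study, 52.36% of the men shown a video in another, and 79.8% of respondents in a third.

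**Working it through.** **1. The plan's own figure.** Inputs from Sample Size and Statistical Power: n = 100, t = 10, a = 2, c = 4, cutoff nta/c ≥ 500.

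100 × 10 × 2 / 4 = 500, so the minimum n is 500 × 4 / (10 × 2) = 100. The stated figure reproduces, with the opt-out left out of a.

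**2. What A-versus-B data identify.** Write V_A and V_B for the utilities of the two tests and V_0 for no test. Conditional on a man's coefficients:

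- P(A over B) = exp(V_A) / [exp(V_A) + exp(V_B)]
- P(tested) = [exp(V_A) + exp(V_B)] / [exp(V_A) + exp(V_B) + exp(V_0)]

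V_0 is absent from the first expression and present in the second. A model fitted to the first kind of data cannot estimate V_0, whatever the sample size.

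**3. Numerical illustration.** Assumptions: 10 tasks, A and B utilities drawn once from a normal distribution with SD 0.8 and then held fixed, Gumbel errors, 20,000 simulated respondents, and V_0 varied.

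| V_0 | Share choosing A over B | Uptake |
|---|---|---|
| −2 | 0.463 | 94% |
| −1 | 0.463 | 85% |
| 0 | 0.463 | 68% |
| 1 | 0.463 | 44% |
| 2 | 0.463 | 23% |

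The utilities are invented. That V_0 is not identified does not depend on them.

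**4. Effect of an attribute level on uptake.** For a single offer, the slope of uptake in utility is P(1 − P). Taking two of the levels above as single-offer probabilities gives 0.94 × 0.06 = 0.056 and 0.44 × 0.56 = 0.246. The same preference weight would move uptake about four times as much in the second case (0.246 / 0.056 = 4.4). So the association named as the main analytic outcome also needs V_0.

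**5. The more generous reading.** Suppose the 1/0 coding is ordinary long format with a third row for no test. With effects-coded attributes only and no constant, a no-test row of zeros has the utility of the average screening profile. Predicted uptake at that average is then 1/(1 + 1) = 50% for one offer and 2/(2 + 1) = 67% for two, whatever the men answered. A no-test constant is needed on this reading too.

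**6. Adding the opt-out under the plan's rule.** With a = 3: 100 × 10 × 3 / 4 = 750, and the minimum n is 500 × 4 / (10 × 3) = 66.7, so 67. The rule shows no shortfall.

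**The case against.** The strongest reply is that the study as a whole can still speak to uptake. The opt-out answers will be collected, so raw uptake can be tabulated and a suitable model can be fitted later. The analysis section is silent on the opt-out rather than excluding it, and an article may leave likelihood details to a fuller plan. The design section refers to a mixed multinomial logit, which does not restrict the model to two alternatives. Table 2 is offered as an example.

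Much of this stands, and it rules out two stronger readings.

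- A reader might infer that uptake cannot be estimated, or that strategies cannot be ranked at all. The documents do not support that. The limit belongs to the stated model, not the data. In a fixed-coefficient logit with a common opt-out utility, uptake rises with a strategy's utility, so A/B weights give the same order. Random coefficients make this approximate.
- A reader might also infer a loss of effective sample size by applying the opt-out shares in Table 1 to the rule of thumb. Those shares are worded as shares of men or respondents, not of choices, and one covers only a video group. In the study with 79.8%, intention to be tested was still 73.5%. Nothing in the protocol says that opt-out tasks are discarded.

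The appeal to a fuller plan does not stand. The article fixes both the dependent and the independent variables, refers to the other alternative in the singular, and uses a = 2. That is a stated analysis that misses its own outcome. The example status of Table 2 covers attributes and levels, which the text leaves to phase 2, but not the response format.

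**Conclusion.** The point holds for the model as written. It supports relative preference weights, marginal rates of substitution and an approximate relative ranking. It does not give uptake probabilities or the effect of attribute levels on them, which is the main analytic outcome. This follows from the algebra and rests on no assumed figure; the 94% to 23% range only illustrates it.

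The conflict between two response stages and one A/B/C question is real, as is the conflict over the primary outcome. All three should be corrected before fielding. The Results section says that no one has yet been recruited into the DCE, so the correction is cheap now, whereas the response format cannot be changed once data are in.

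**What to change.** - **Format.** Settle one response format and make the text and Table 2 agree. Either format identifies uptake if the opt-out is modelled. The two-stage format has the advantage of keeping the A/B answer when the man opts out.
- **Model.** Make the primary analysis a panel mixed logit over A, B and no test, with an alternative-specific constant for no test (a mean and, if random, an SD).
- **Likelihood under two stages.** Use both answers. One way, conditional on the coefficients: a man who picks A and would be tested contributes P(A from A, B, no test). A man who picks A and would not be tested contributes P(no test from all three) × P(A from A, B). Coding the second man only as choosing no test would discard his A/B answer.
- **Design.** Put the no-test alternative and its constant into the Ngene utility specification.
- **Outcome.** Derive predicted uptake from this model, and name the same primary outcome in Primary and Secondary Outcomes and in DCE Data Analysis.

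The cost is one or two extra parameters, a revised design specification and a redrawn table. By the plan's own rule (750 against 500 at n = 100) the sample size need not rise. That rule is a rule of thumb for mean preferences and says nothing about the precision of predicted uptake.
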